#### Intervention Assessments and Other Measures

Table 1 shows a list of self-report measures, including primary and secondary outcomes, demographics, and covariates. Primary and secondary outcomes and content-specific measures will be assessed at baseline and in all follow-up surveys. Measures will be adapted for weekly diary assessments along with items related to daily drinking context, consistent with our prior work. We anticipate baseline and follow-up surveys to be approximately 20 minutes in length, and daily surveys will be 5 minutes in length. Participants will be made aware of the importance of the data, the confidential nature of their responses, and we will follow procedures to secure their privacy.

**Table 1 table1:** Self-report measures.

Construct		Description
**Primary outcomes**		
	Alcohol-related sexual behavior	Number of times that alcohol was consumed during or before sex, quantity of alcohol consumed before sex [79]
	Alcohol-related consequences—sexual	Sexual consequence scale [80]
**Secondary outcomes**		
	Alcohol use behavior	Daily drinking questionnaire [81], heavy-episodic drinking, and high-intensity drinking
	Alcohol-related consequences—nonsexual	Young adult alcohol consequences questionnaire [82]
	Sexual behavior	Frequency of sex (including oral, vaginal, or anal), number of casual sexual partners, and number of times that a condom was used during sex [79,83]
**Demographics and covariates**		
	Background demographics	Birth sex, gender identity, sexual orientation, race and ethnicity, height and weight (for blood alcohol content calculation)
	Alcohol use history	Lifetime alcohol use, age of drinking and intoxication onset, and family history
	Sex history	Age of first sex and history of sexual behavior

In addition to self-report measures, participant behavior analytics will be captured to help ensure intervention fidelity and be included as covariates in analyses. Analytics include (1) whether or not participants accessed their PFI, CDF, or GHI; (2) the number of times each PFI, CDF, or GHI was accessed; (3) time spent viewing each PFI, CDF, or GHI; and (4) time spent viewing each topic area within the PFI, CDF, or GHI. These data will be captured through tracking routines programmed on the website. We will examine the depth of college students’ engagement with intervention content to assess the effects of program exposure (ie, dose) based on the level of access to content (eg, ranging from students who looked at PFIs and all weekly CDF and GHI content vs those who engaged in some or none of the content) and time spent on various intervention components. These data will provide intervention acceptability metrics and allow us to control each participant’s exposure to the PFI, CDF, or GHI content in outcome analyses.

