### Effectiveness Trial (Phase 2)

#### Overview of RCT Design

We will conduct a multisite, 4-group RCT to evaluate the intervention (Figure 2). Participants (N=600 total, 300 per site) will be randomized to 1 of 4 groups: (1) PFI+CDF with weekly diary surveys; (2) PFI+GHI (generic health information) with weekly diary surveys; (3) PFI-only, no weekly diary surveys; and (4) AOC, no weekly diary surveys. All participants will complete a baseline survey during the first week of the semester, be randomly assigned to 1 of the 4 groups, and complete follow-up surveys at 1, 2, 3, 6, and 13 months post baseline. The staggered design allows for comparison of the enhanced PFI+CDF relative to the PFI+GHI, which may be consistent with a “treatment-as-usual” comparison group (eg, of the universities that have adopted an evidence-guided alcohol intervention program for their campus, many currently deliver commercialized alcohol-focused PFIs to incoming first-year students) [35,36]. Providing weekly GHI in the comparison group allows for an equal number of “exposures” between PFI+CDF and PFI+GHI, analogous to an attention control group, offering a clearer understanding of the overall impact of the PFI+CDF adaptation. The inclusion of 2 PFI conditions, 1 with weekly diary assessments and 1 without, allows us to control potential assessment reactivity that might result from the diary-style assessment approach. This design is intended to allow a separation of the “true” intervention effect of the CDF above and beyond the effect of assessment reactivity. The PFI-only versus AOC group comparison will provide a test of the integrated PFI that has been adapted based on stakeholder feedback.

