#### Procedures

Following the baseline survey, participants randomized to 1 of the 3 PFI conditions will immediately be linked to their PFI, which will also be sent via email and SMS text message. A 2-week window is allotted at the beginning of the semester for participants to complete their baseline assessment and, if applicable, view their PFI content. Following that period, participants in the PFI+CDF and PFI+GHI will be sent prompts via email and SMS text message to complete diary surveys on Friday through Monday of each week. On Tuesdays, participants in the PFI+CDF group will receive a link to access their CDF corresponding to that week’s behavior, via text and email, and those in the PFI+GHI group will receive a link to access health topics relevant to college students guided by the American College Health Association website (eg, nutrition, mono, exercise, and immunizations) [78]. These procedures will continue for a total of 12 weeks. All participants will be asked to complete web-based 1-, 2-, 3-, 6-, and 13-month follow-up assessments and receive up to US $100 (US $15 per survey, with an additional US $10 bonus for the 13-month follow-up). Participants in the diary conditions will receive an additional payment up to US $96 (US $2 per day×4 days×12 weeks=US $96).

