#### Statistical Analysis

For study phase 2, we will use a multilevel model for the main outcome analysis where the participant is defined at the highest level of the model (level 2), and observations (level 1) are nested within the participant. We will assume that the observation-level (level 1) residual error term and participant-level (level 2) intercept coefficients (ie, random effects) are each normally distributed with mean zero and a variance that is estimated from the data, while intercept and slope coefficients are multivariate normally distributed with mean zero for each, and a covariance matrix that is estimated from the data. Intervention groups will be tested as a fixed effect. Given that many outcomes of our interest are count outcomes with excessive zeros, we will utilize appropriate models to accommodate a zero-inflated outcome distribution with overdispersion [44,84]. The 2 sites can be entered as a random effect (level 3) or a fixed effect in a 2-level model. We will include an interaction term to test whether PFI+CDF is similarly effective for men and women. The intercept and growth slopes will be appropriately specified to maximize information.

We will use a parallel process growth model to test the codevelopment of correlated processes (eg, alcohol use and RSB) and a parallel process growth mediation model. This allows for the examination of 2 potentially dependent reduction trajectories, which are altered by intervention. We expect that those who reduce alcohol misuse more rapidly in response to intervention will also exhibit a trajectory in which one’s likelihood of engaging in RSB decreases, which can be tested by comparing a model where the 2 slope terms are correlated with a null model where its correlation is constrained to be zero. Intervention effects can be explicitly tested by adding intervention membership as an external covariate that changes these coupled processes. Intervention effect modifiers or moderators will be tested in a confirmatory (eg, sex) or exploratory investigations.

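### Engagement measured after randomisation is named as a covariate for the outcome analyses, and nothing keeps it out of the main group comparison

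*Protocol article*

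**What the plan says.** The commitment is in the paragraph after Table 1, under Intervention Assessments and Other Measures. It opens by saying that "participant behavior analytics will be captured to help ensure intervention fidelity and be included as covariates in analyses". It lists four kinds of tracking data: whether content was opened, how often, total viewing time, and viewing time by topic. It closes by saying that these data will "allow us to control each participant’s exposure to the PFI, CDF, or GHI content in outcome analyses". Between these statements it describes a separate use of engagement, "to assess the effects of program exposure (ie, dose) based on the level of access to content".

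The Procedures section fixes the timing: "participants randomized to 1 of the 3 PFI conditions will immediately be linked to their PFI". CDF or GHI links then follow weekly for 12 weeks. AOC receives no content, and PFI-only receives neither CDF nor GHI.

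The Statistical Analysis section describes the main multilevel model. On the comparison itself it says: "Intervention groups will be tested as a fixed effect". It goes on to site, random intercepts and slopes, zero-inflation and an interaction with sex. It does not mention engagement, either to include it or to leave it out.

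**The concern.** Viewing is something that assignment causes. A model that holds viewing constant no longer estimates the effect of being offered the intervention, and the first aim of the trial is to evaluate that impact.

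Two problems follow:

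- **Mediation.** If the intervention works because students read the feedback, adjusting for reading removes that part of the effect.
- **Self-selection.** Students choose how much to view. If a trait such as motivation affects both viewing and later behaviour, conditioning on viewing brings back the confounding that randomisation had removed.

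For contrasts with AOC there is a structural difficulty as well. Exposure there is zero or undefined for everyone, so the group coefficient is an extrapolation to a treated student who viewed nothing.

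**Working it through.** **The plan's own figure.** Sample Size Justification gives power of at least 0.89 for the three PFI arms against control, with effect size 0.3 and alpha .05. The article gives 600 participants in four groups. I assume equal allocation (150 per arm) and a two-sided test, because neither is stated. The contrast is then 450 against 150:

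- SE = √(1/450 + 1/150) = 0.0943
- power = Φ(0.30/0.0943 − 1.96) = Φ(1.22) = 0.889

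The stated 0.89 is reproduced, and it describes the comparison without engagement adjustment.

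**What adjustment does against AOC.** With exposure E coded 0 in AOC, the slope b on E is estimated only within the PFI arms, and least squares gives

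adjusted effect = unadjusted effect − b × (mean E in the PFI arms).

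Assumptions, none of them from the article:

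- E is the fraction of content viewed, with mean 0.6 and SD 0.2.
- The outcome is continuous with SD 1, and lower is better.
- Where a trait is included, it correlates √0.5 with viewing and 0.3 with a better outcome.

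The slope is the sum of two parts:

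- If a share s of the −0.30 effect runs through viewing, that part is b = −0.30s/0.6: 0 (none), −0.25 (half) or −0.50 (all).
- The trait adds −0.3 × √0.5/0.2 = −1.06.

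Simulation (4,000 runs per row, ordinary least squares) agrees with the formula:

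| True effect | Share through viewing | Trait link | Unadjusted estimate (rejection) | Adjusted, formula | Adjusted, simulated (rejection) |
|---|---|---|---|---|---|
| −0.30 | none | no | −0.30 (0.88) | −0.30 | −0.30 (0.40) |
| −0.30 | half | no | −0.30 (0.90) | −0.15 | −0.15 (0.14) |
| −0.30 | all | no | −0.30 (0.89) | 0.00 | 0.00 (0.05) |
| −0.30 | none | 0.3 | −0.30 (0.90) | +0.34 | +0.35 (0.54) |
| −0.30 | all | 0.3 | −0.30 (0.89) | +0.64 | +0.64 (0.96) |
| 0 | – | 0.3 | 0.00 (0.05) | +0.64 | +0.65 (0.97) |

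Rejections in the last three rows point towards harm.

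The first row loses power without bias because group and exposure are nearly collinear. The variance gains 0.6² × 1/(450 × 0.2²) = 0.020. The SE becomes √(0.0089 + 0.020) = 0.170, and power is Φ(0.30/0.170 − 1.96), about 0.42.

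The direction of the confounding is also an assumption. If higher-risk students view more, the trait term changes sign. With no effect through viewing, the adjusted estimate is then −0.30 − 1.06 × 0.6 = −0.94, an exaggerated benefit.

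**PFI+CDF versus PFI+GHI, 150 per arm.** Both arms have content to view. With viewing standardised to SD 1, the formula becomes

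adjusted effect = unadjusted effect − b × (difference in mean viewing).

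- Equal viewing: the difference is 0 and there is no bias. Simulated −0.30 before and after adjustment.
- CDF viewed 0.5 SD more, trait as above: b = −0.3 × √0.5 = −0.21, so −0.30 + 0.21 × 0.5 = −0.19. Simulated −0.20, with power falling from 0.74 to 0.39. Under a true null the simulated estimate is +0.11 and rejection is 15%.
- CDF viewed 0.5 SD less: the same arithmetic gives −0.30 − 0.11 = −0.41, and −0.11 under the null, a false benefit.

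**The case against.** The strongest reply is that the only section specifying the main model does not contain these covariates. On its face, Statistical Analysis compares assigned groups. The commitment to adjust sits in a measures section that speaks of analyses and outcome analyses without saying which, and the same paragraph describes a dose examination, where exposure terms belong. The article also never says that AOC will be coded zero and entered in a four-arm model with these terms.

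Much of this stands. A reader might infer that the trial's main conclusion will be invalid. The article does not support that, because the main model may well omit the analytics. A reader might also infer that the bias has a known direction whatever is assumed. It does not: for PFI+CDF versus PFI+GHI it can be absent or take either sign, and against AOC it depends on who views more. The simulated sizes are illustrative. They use one continuous outcome, not the planned multilevel model for zero-inflated counts.

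The reply does not remove the point. The dose examination is described in its own sentence, and control of exposure in outcome analyses is then stated as a further use. Nothing confines that use to exploratory models, and Statistical Analysis does not reserve an unadjusted randomised comparison as primary. This is also not detail left to a later plan. It is a stated rule, and an analysis plan that followed it would carry it forward.

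**Conclusion.** The point holds as a conditional one. The article twice names post-randomisation engagement as a covariate, once expressly for outcome analyses, and leaves open whether the main group effect is so adjusted.

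For contrasts with AOC, the change of meaning to an effect at zero viewing follows from the design once exposure is entered as zero there. It does not depend on the simulation inputs. Its numerical consequence does: with a true −0.30 SD and no confounding, the adjusted estimate lies between −0.30 with power about 0.4 and 0.00 with no power beyond alpha. With an assumed trait correlation of 0.3, the sign can reverse. For PFI+CDF versus PFI+GHI, harm requires both a difference in viewing between arms and a link between viewing and outcome.

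The wording should be settled before analysis, because the ambiguity concerns which effect the trial estimates.

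**What to change.** Amend the paragraph under Intervention Assessments and Other Measures, and add a matching statement to Statistical Analysis. Suggested wording: *The primary and secondary effectiveness analyses compare participants by assigned group and adjust only for variables measured before randomisation. Engagement analytics are used to describe fidelity and acceptability, and in a dose analysis reported as secondary and observational.* The dose examination that the article already describes is kept, with a label.

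If a complier-average effect with assignment as instrument is wanted, limit it to contrasts where assignment plausibly acts only through viewing. PFI-only versus AOC is an example, since neither arm keeps diaries. Overview of RCT Design itself raises reactivity to the diary assessments. That is a route from assignment to outcome that bypasses content, so the assumption fails for diary versus non-diary arms.

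The cost is about two sentences of wording and no new data.

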#### Sample Size Justification

Power analyses to detect intervention main effects were conducted using Optimal Design Plus Version 3.01 software and the “power determination approach.” Based on past research, we assumed a standardized effect size of 0.3 (a small to medium effect size) from the repeated measures RCT with 5 follow-ups over 13 months. To examine the effect of the PFI+CDF and PFI interventions, compared to the control, a minimum of 452 participants are required for a power of 0.8 at an alpha level of .05. To examine the effect of the PFI+CDF intervention (vs PFI+GHI or PFI-only intervention), at least 350 participants are required. Based on this power analysis, there is sufficient power (≥0.89) to detect a small to medium effect size for the integrated interventions (PFI+CDF, PFI+GHI, and PFI only) versus control and sufficient power to detect the small effect of the PFI+CDF intervention compared to the PFI+GHI or PFI-only intervention over time. Although the overall effect size was conservatively assumed to fall between small and medium in size, due to the fine-grained assessment approach within the time period where most changes are likely to occur, followed by a long-term 13-month follow-up assessment, we anticipate that the proposed study is sufficiently powered.

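### The 350 required for PFI+CDF against another PFI arm reproduces as a two-arm total, but each pair holds about 300, and the claim of power for a small effect is unsupported

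*Protocol article*

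**What the plan says.** All figures are in the protocol article.

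- Overview of RCT Design: "Participants (N=600 total, 300 per site) will be randomized to 1 of 4 groups". No allocation ratio is given.
- The same section describes PFI+CDF versus PFI+GHI as a contrast in its own right. Weekly generic health information "allows for an equal number of “exposures” between PFI+CDF and PFI+GHI, analogous to an attention control group". It adds that having two PFI conditions, one with diaries and one without, is meant to separate the effect of the dynamic feedback from reactivity to the diaries.
- Sample Size Justification, assumption: "we assumed a standardized effect size of 0.3 (a small to medium effect size) from the repeated measures RCT with 5 follow-ups over 13 months".
- Active interventions against control: "a minimum of 452 participants are required for a power of 0.8 at an alpha level of .05".
- PFI+CDF against the other PFI arms: "To examine the effect of the PFI+CDF intervention (vs PFI+GHI or PFI-only intervention), at least 350 participants are required".
- Conclusion drawn for the contrast with control: power of at least 0.89 for a small-to-medium effect of the three PFI arms taken together.
- Conclusion drawn for the dynamic-feedback contrast: "sufficient power to detect the small effect of the PFI+CDF intervention compared to the PFI+GHI or PFI-only intervention over time". This statement carries neither a power value nor an effect size.

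**The concern.** The question that separates this trial from earlier PFI work is whether dynamic feedback adds anything to a PFI. PFI+CDF versus PFI+GHI answers it most cleanly, because both arms complete diaries and receive weekly contact. If 350 participants are needed for that pair and only 300 are in it, the section claims a power that its own figures do not give.

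The wording also moves from a small-to-medium effect, the only one assumed, to a small effect, for which nothing is calculated. The one power value in the section belongs to a different contrast, and a reader could carry it over to the dynamic-feedback comparison. A null result there might then be read as good evidence of no added benefit when the trial had only moderate power to find the assumed effect.

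**Working it through.** **Inputs.** From the article: N = 600, four groups, standardized effect d = 0.3, power 0.80, alpha .05. Assumed: equal allocation (150 per arm) and a two-sided test, since neither is stated. The normal quantiles are 1.960 and 0.842, and (1.960 + 0.842)² ≈ 7.849.

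**Step 1: reproduce the 350.** For allocation 1:k, total N = [(1+k)²/k] × 7.849 / d².

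- 1:1 gives 4 × 7.849 / 0.09 = 348.8, or 175 per arm and **350** in total: an exact match.
- 1:2 (PFI+CDF against the two other PFI arms pooled) gives 4.5 × 7.849 / 0.09 = 392.4, or 393 rounded up by arm: no match.
- 1:1 with a one-sided test gives 276: no match.

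**Step 2: check the other figures.**

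- 1:3 (control against three pooled arms) gives (16/3) × 7.849 / 0.09 = 465.1. The stated 452 is close but is not reproduced.
- Power for 150 vs 450 at d = 0.3: 0.3 / √(1/150 + 1/450) − 1.960 = 3.182 − 1.960 = 1.222, giving 0.889. This agrees with the stated ≥0.89 to two decimals, with all 600 analysed.

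**Step 3: power for one pair, 150 vs 150.** The standard error is √(2/150) = 0.1155.

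- d = 0.3: 0.3 / 0.1155 − 1.960 = 0.638, power **0.738** (0.736 with the exact t distribution).
- Effect detectable with 80% power: 2.802 × 0.1155 = **0.32**.
- Scaling from the protocol's own 350, without assuming an outcome model: 2.802 × √(300/350) − 1.960 = 0.634, power 0.737. The answer is the same.

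**Step 4: the pooled reading, 150 vs 300.** The standard error is √(1/150 + 1/300) = 0.100.

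- d = 0.3: 3.00 − 1.96 = 1.04, power **0.851**.
- Scaling from 350 to 450: 2.802 × √(450/350) − 1.960 = 1.217, power 0.888.

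**Step 5: a small effect.** The article gives no value, so 0.2 is an assumption here.

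- Pairwise: 0.2 / 0.1155 − 1.960 = −0.228, power **0.41**.
- Pooled: 2.00 − 1.96 = 0.04, power **0.52**. Scaling from 350 gives 2.802 × (0.2/0.3) × √(450/350) − 1.960 = 0.158, power 0.56.
- Between the two, at d = 0.25, power is 0.58 pairwise and 0.71 pooled.

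**The case against.** **The 350 may not be a pairwise figure.** The sentence can be read as PFI+CDF against the other two PFI arms together, parallel to the preceding sentence on the PFI interventions against control. That contrast has 450 participants, and power at 0.3 is adequate. The stated ≥0.89 does not exclude this reading: scaling 452 to 600 gives 0.898 and scaling 350 to 450 gives 0.888. For the same reason, ≥0.89 is consistent with equal allocation but does not prove it. This part of the objection stands, so it would go too far to infer that every reading of the section is short of power. Against it, 350 matches a 1:1 contrast and not a 1:2 contrast, the text does not say that the arms are pooled, and pooling would undo the separation of diary from no-diary arms.

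**The calculation was for repeated measures in dedicated software.** The simple formula does not reproduce 452, so the figures above should not be taken as the software's output. Averaging five follow-ups can raise power. With an assumed within-person correlation of 0.7 and an effect standardized to a single-time SD, 150 vs 150 gives 0.85 at d = 0.3. Under those same assumptions, however, the required total would be 266 and not 350. Such a gain therefore cannot reconcile 300 with a stated minimum of 350; it can only replace the 350, with its assumptions shown.

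**Small may be loose wording for 0.3.** It may be. The sentence should then say 0.3, because as written it claims more than was calculated.

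**Attrition.** A reader might infer that loss over 13 months makes the shortfall much worse. The article gives no rate, and an article may leave this to the full protocol. Removing an assumed 10% or 20% of participants entirely would give pairwise power of 0.69 or 0.64. The planned multilevel model would keep the earlier observations of those lost later, so these values are worst-case illustrations and not part of the finding.

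**Conclusion.** The section is wrong as written on two counts.

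1. For PFI+CDF versus PFI+GHI, and likewise versus PFI-only, the protocol's own requirement of 350 is not met by a pair of 300. Power at the assumed effect is about 0.74 against a target of 0.80. The shortfall is moderate: the detectable effect is about 0.32 against 0.30. This rests on equal allocation, a two-sided test and the pairwise reading of 350, which its arithmetic favours without proving.
2. The claim of power for a small effect is unsupported by anything stated on either reading, at about 0.41 pairwise and 0.52 to 0.56 pooled for an assumed 0.2. This is the more serious of the two.

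A reader might infer that the trial is too small and must grow. The documents do not support that. The pooled contrasts are adequately powered at 0.3, and repeated-measures assumptions not shown in the article could raise the pairwise figure.

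**What to change.** Revise Sample Size Justification as follows.

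- State which contrast the 350 refers to. If PFI+GHI and PFI-only are pooled, say so and explain how that fits with keeping the diary and no-diary arms apart.
- State the allocation ratio and give power by contrast, for example: *With 150 participants per arm, power is about 0.74 at a standardized effect of 0.3 for PFI+CDF versus PFI+GHI and for PFI+CDF versus PFI-only; the effect detectable with 80% power is about 0.32.* Alternatively, give the repeated-measures assumptions that support a higher figure, and restate the required number on the same basis.
- Label ≥0.89 as applying to the three pooled PFI arms versus control with all 600 analysed.
- Replace the reference to a small effect with the assumed 0.3.
- If attrition is shown, present it as a worst-case illustration under assumed rates.

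The cost is wording only. N does not change, and the stated power for the key comparison becomes slightly less favourable. Having 350 in every pair under equal allocation would take 4 × 175 = 700 participants, which this point does not ask for.

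### The stated power of at least 0.89 belongs to all three PFI arms pooled against control; the two-arm contrasts the design relies on have about 0.74 on the same basis

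*Protocol article*

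**What the plan says.** Overview of RCT Design randomizes 600 students to four arms. PFI+CDF and PFI+GHI have weekly diary surveys; PFI-only and the assessment-only control (AOC) have none. The section gives each comparison a purpose. For the PFI: "The PFI-only versus AOC group comparison will provide a test of the integrated PFI that has been adapted based on stakeholder feedback". Having one PFI arm with diaries and one without "allows us to control potential assessment reactivity that might result from the diary-style assessment approach", and PFI+GHI matches PFI+CDF on number of exposures, so that the CDF effect can be separated from reactivity.

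Sample Size Justification states its basis as "we assumed a standardized effect size of 0.3 (a small to medium effect size) from the repeated measures RCT with 5 follow-ups over 13 months". For intervention versus control, "a minimum of 452 participants are required for a power of 0.8 at an alpha level of .05". For PFI+CDF against PFI+GHI or PFI-only, "at least 350 participants are required". It concludes that power is sufficient, at 0.89 or more, to "detect a small to medium effect size for the integrated interventions (PFI+CDF, PFI+GHI, and PFI only) versus control", and that power is also sufficient for PFI+CDF against PFI+GHI or PFI-only.

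Statistical Analysis enters intervention group as a fixed effect and does not mention combining arms.

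**The concern.** The two sections describe different comparisons. The design section relies on two-arm contrasts in which both arms have diaries or neither has. The sample-size section attaches its only numerical power claim to three arms taken together against control. A reader would naturally take 0.89 as covering the test of the PFI, but it covers a comparison of any PFI package with control, with more participants and a mixture of exposures. If the power of the named contrasts is lower, the sample size is justified for a question that the design section does not pose, and a null result for PFI-only versus AOC or for PFI+CDF versus PFI+GHI would be less informative than the protocol implies.

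**Working it through.** **Inputs.** From the protocol: effect 0.3 in SD units, alpha .05, target power 0.8, 600 participants, four arms. Assumed: two-sided testing, and equal allocation (150 per arm), since no ratio is stated. The protocol gives no correlation or dropout figure, so the first pass uses neither.

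**Formulas (SD = 1).** SE = √(1/n₁ + 1/n₂). Power = Φ(0.3/SE − 1.96). Total N for 80% power with comparison ratio 1:k is (1 + k)(1 + 1/k)·((1.960 + 0.842)/0.3)², where the squared term is 87.2.

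**Step 1: reproduce 0.89.**

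| Layout | SE | Power |
|---|---|---|
| 450 vs 150 (three PFI arms vs AOC) | 0.0943 | 0.889 |
| 300 vs 150 | 0.1000 | 0.851 |
| 150 vs 150 | 0.1155 | 0.738 |

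Only the first row matches. As a cross-check, scaling the protocol's 80% power at 452 up to 600 participants gives 0.898, which also requires all 600 to be in the contrast.

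**Step 2: reproduce 452 and 350.**
- Ratio 1:3: 4 × (4/3) × 87.2 = 465. The stated 452 is within 3% of this; 113 versus 339 has power 0.789.
- Ratio 1:1: 2 × 87.2 = 174.4, so 175 per arm and 350 in total, exactly as stated. Ratio 1:2 would need 393.

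So 452 fits the pooled layout approximately, and 350 is a two-arm total.

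**Step 3: apply the same basis to the contrasts the design names.**
- PFI-only vs AOC, 150 vs 150: 0.3/0.1155 − 1.96 = 0.638, power 0.738.
- PFI+CDF vs PFI+GHI, or vs PFI-only, each 150 vs 150: also 0.738. Two arms hold 300 participants against the protocol's own 350. The total exceeds 350 only if both comparators are combined (150 vs 300, power 0.851), and then half of the comparator has no diaries.
- Effect detectable with 80% power at 150 per arm: 2.802 × 0.1155 = 0.323.

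**Step 4: what the pooled contrast contains.** Under equal allocation, 300 of the 450 pooled participants are asked for 4 days × 12 weeks = 48 diary surveys, and AOC for none. The contrast therefore combines PFI, CDF or GHI content, and diary exposure.

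**Step 5: sensitivity.** With assumed dropout of 10%, 20% and 30%, the 0.738 becomes 0.69, 0.64 and 0.59. In the other direction, if the endpoint were the mean of five follow-ups with an assumed within-person correlation r, the variance factor is (1 + 4r)/5: 0.60 at r = 0.5 and 0.76 at r = 0.7, giving power of 0.92 and 0.85 before dropout.

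**The case against.** The strongest reply is that the sample-size section makes a power statement and does not define an analysis. It calls the pooled contrast a comparison of the integrated interventions with control, which is a legitimate question, and it does not call it the PFI effect. The design section already names the PFI test, and detailed contrasts are commonly left to an analysis plan that is not shown. This stands, and it limits the point to the power claims.

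A reader might go further and infer that the trial's PFI effect will be confounded with diary reactivity. The documents do not support that. No section says the outcome analysis will pool arms. PFI-only versus AOC has no diaries on either side, and PFI+CDF versus PFI+GHI has them on both, so the separation the design promises is still available. Diary effects of 0.05, 0.10 and 0.20 SD (assumed; the protocol gives no figure) would shift the pooled contrast by two thirds of that, 0.033, 0.067 and 0.133 SD. This matters only if the pooled result is credited to the PFI alone, which the protocol does not propose. Nor should the word joining PFI+GHI and PFI-only in the second power claim be read as pooling, since 350 is the 1:1 total. The remark likening PFI+GHI to usual practice can be debated, but no analysis depends on it.

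A second reply is that five follow-ups raise power. They could, as Step 5 shows. But 350 and 0.89 both reproduce without any such gain, so the stated figures do not appear to include one, and no correlation is given from which to claim it. Fitting all four arms in one model does not remove the shortfall either: the precision of a two-arm contrast still depends on the sizes of those two arms.

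**Conclusion.** The power claims do not cover the contrasts the design relies on. The 0.89 is for three arms pooled against control. The named PFI test, and the pairwise PFI+CDF comparisons, each have about 0.74 at an effect of 0.3, below the protocol's 0.8 target. The PFI+CDF pair also has 50 participants fewer than the protocol's own minimum. This rests on equal allocation, two-sided alpha, no dropout and no repeated-measures gain. The last three of these are consistent with how 350 and 0.89 reproduce. The shortfall is moderate and could disappear under a stated, defensible correlation. The point is a mismatch between the power statement and the design; it does not show a confounded analysis.

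**What to change.** In Sample Size Justification, tie the power statement to the contrasts in Overview of RCT Design: PFI+CDF versus PFI+GHI for the CDF effect, and PFI-only versus AOC for the PFI effect. State the allocation ratio and sidedness. Give power for each contrast as about 0.74 at 0.3, with 80% power at about 0.32, before dropout. Alternatively, state the repeated-measures correlation and endpoint definition that would raise it. Keep the pooled three-arm contrast as a secondary comparison of any PFI package with control, and say that it is not attributed to the PFI alone.

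This is a change of text. Its cost is that the stated power becomes less favourable. Keeping 80% power at 0.3 on the present basis would take 175 per arm, or 4 × 175 = 700 participants in four equal arms, so the sponsor would have to accept the lower power, justify a gain from repeated measures, or enlarge the trial.
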